#### Other indicators and safety assessment indicators

2.12.2

Statistical analysis is performed using SPSS V25.0 software. Continuous variables that conformed to a normal distribution or approximate normal distribution are expressed as mean ± standard deviation ($\bar{x}\,s$), while those that do not conform to a normal distribution are expressed as median and interquartile range [M (P25, P75)]. Categorical variables are described using frequency or percentage. Comparisons between groups of unordered categorical variables are performed using the chi-square test. The incidence of silent aspiration will be compared between groups using Fisher’s exact test. Additionally, PAS scores ≥ 5 will be analyzed as ordinal variables using the Mann-Whitney U test.

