### Inclusion criteria

2.3

Patients are eligible for study inclusion if they meet all of the following:

(1)   Fulfill the diagnostic criteria for acute ischemic stroke as defined by the Chinese Guidelines for the Diagnosis and Treatment of Acute Ischemic Stroke (2023 Edition) (14), and have dysphagia confirmed by the Scottish Intercollegiate Guidelines Network (SIGN) recommendations (15).(2)   Age between 18 and 80 years.(3)   FOIS levels between 2 and 4.(4)   Stroke duration of 15–180 days.(5)   Infarction location in the cerebral cortex and subcortical regions.(6)   Patients or their legal guardians must fully understand the study procedures, provide written informed consent, and agree to participate.

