### Sample size, randomization, and blinding

2.7

The primary efficacy outcome is the FOIS score. As neither our team nor previous studies have used this measure to assess acupuncture efficacy for post-stroke dysphagia, it is not possible to determine an appropriate effect size from existing data. A review of similar studies has revealed that after 4 weeks, the FOIS score difference from baseline was 1.31 (rehabilitation training group) vs. 0.31 (sham training group), with a standard deviation of 1.09 (16). This value will be used as the expected effect size for this trial, and sample size calculations will be conducted based on a superiority trial design (17). These parameters (μA = 1.31, μB = 0.31, σ = 1.09, α = 0.05, power = 0.8, δ = 0.39) were applied in a superiority design with 1:1 allocation. After calculation, nA = nB = 40. Considering a 20% dropout rate, this study is expected to enroll 100 patients.

Randomization will use computer-generated numbers to allocate patients equally to acupuncture or rehabilitation groups. A stratified block randomization design will be employed. An independent statistician will generate all random sequences in SPSS 25.0, with study center and baseline FOIS as stratification factors, block lengths of 4 and 6 randomly interleaved, and the seed number set to 20240420. Allocation concealment will be implemented through sequentially numbered, opaque, sealed envelopes kept by a research coordinator who has no conflicts of interest with the study team. After participants have completed baseline assessments and provided written informed consent, the responsible physician will open the corresponding envelope on-site to reveal the allocation. The statistician generating the random sequence will operate independently of the coordinator handling allocation concealment. Neither patients nor physicians will know the allocation in advance. All participants will be followed for 90 days.

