##### Swallowing safety and efficacy: Fiberoptic Endoscopic Evaluation of Swallowing

2.9.2.4

FEES serves as a well-established and reliable tool for assessing swallowing impairment and guiding behavioral interventions (39). During the procedure, a clinician passes a flexible fiberoptic endoscope transnasally to directly visualize the structural integrity of the oropharynx and larynx, while dynamically observing key physiological events such as bolus transit, glottic closure, and laryngeal elevation. These observations provide a quantitative basis for grading the severity of swallowing dysfunction. Swallowing safety is evaluated using the Penetration-Aspiration Scale (PAS) (40), whereas swallowing efficacy is measured with the Yale Pharyngeal Residue Severity Rating Scale (YPRSRS) (41). Both instruments offer objective metrics that help minimize subjective assessment bias and support the development of individualized treatment plans.

To detect silent aspiration during Fiberoptic Endoscopic Evaluation of Swallowing (FEES), the endoscope will be maintained in position for an extended observation period of 45 s following each bolus swallow, allowing for the active capture of delayed aspiration events. Even in the absence of immediate aspiration, the presence of subglottic residue—observed as retained material or contrast-stained liquid below the vocal folds—will be documented as indirect evidence of silent aspiration. For precise quantification, the Penetration-Aspiration Scale (PAS) will be applied with specific grading annotations; for instance, “PAS 5 with thin liquids” will be recorded instead of the generic “PAS 5.” Furthermore, the incidence of silent aspiration will be statistically analyzed separately, and its association with the Functional Oral Intake Scale (FOIS) scores will be examined to reduce bias in therapeutic outcome evaluation.

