### Evaluation schedule

2.10

FOIS, NIHSS, SWAL-QOL, PAS, and YPR-SRS will be assessed at baseline (pre-treatment), 15 and 30 days after treatment initiation, and 30 and 60 days post-treatment completion. Additionally, fMRI-derived ReHo and ALFF metrics, sEMG evaluations, and PRO scores will be obtained at baseline and at 15 and 30 days following treatment initiation. The study timeline for enrollment, intervention, and assessment is detailed in Table 4. All dropouts and their respective reasons will be systematically documented in the case report forms (CRFs).

**TABLE 4 T4:** Study assessment schedule.

Times outcomes	Before treatment	Treatment				Follow-up	
	Day 3–0	Week 1–2	(Day 15)	Week 2–4	(Day 30)	Day 60	Day 90

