#### Statistical control for confounding factors

2.12.5

Potential confounders, including age, sex, PSD duration, baseline NIHSS and FOIS scores, stroke subtype, comorbidities (hypertension, diabetes), total treatment expectation scores, and the Deqi Index (DQI), will be accounted for in the analyses. For primary and secondary efficacy outcomes, repeated-measures mixed-effects models or multiple linear regression will be employed. Stroke subtypes will be examined using stratified analysis, while comorbidities will be assessed via sensitivity analyses.

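### The Fisher's exact test for silent aspiration leaves the baseline FEES result unused; stratifying by it would cost nothing and make this secondary safety comparison more efficient and easier to interpret

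*Protocol article*

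**What the plan says.** Section 2.12.2 names one test for this endpoint: "The incidence of silent aspiration will be compared between groups using Fisher’s exact test". Section 2.9.2.4 places it among the FEES outcomes, says that "the incidence of silent aspiration will be statistically analyzed separately", and adds that its association with FOIS will be examined to limit bias in judging efficacy. The same section names PAS as the measure of swallowing safety.

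Baseline FEES information exists. Section 2.10 says: "FOIS, NIHSS, SWAL-QOL, PAS, and YPR-SRS will be assessed at baseline (pre-treatment), 15 and 30 days after treatment initiation", and the two follow-up visits come after that. The section 2.9.2.4 procedure for detecting silent aspiration applies to FEES generally, so I take it that baseline status will be known.

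Entry requires confirmed dysphagia and "FOIS levels between 2 and 4". Neither the inclusion nor the exclusion criteria rule out silent aspiration at entry. Randomisation is stratified "with study center and baseline FOIS as stratification factors", so baseline aspiration is balanced only by chance. Section 2.12.5 lists baseline NIHSS and FOIS among its covariates but not baseline PAS or silent aspiration. Its models are mixed-effects models or multiple linear regression for efficacy outcomes.

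**The concern.** A patient who aspirated silently before treatment and still does carries a different message from one who began to do so on treatment. The first is a failure to resolve, the second a possible harm. A plain two-by-two table of later status by arm cannot tell them apart, and the named test cannot use the baseline result that would.

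There is also a cost in precision. If baseline status predicts later status, most of the variation in the endpoint is already explained before treatment starts, and an unadjusted test leaves it in as noise. The protocol singles out silent aspiration so that a gain in oral intake is not accepted when unnoticed aspiration lies behind it. A comparison that detects little and mixes two kinds of case serves that purpose poorly.

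**Working it through.** **The plan's own figure.** The only sample-size figure is for FOIS (section 2.7). With difference 1.31 − 0.31 = 1.00, margin 0.39, SD 1.09, power 0.8 and one-sided α 0.05:

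n per arm = 2 × (1.645 + 0.842)² × 1.09² / (1.00 − 0.39)² = 39.5, so 40; and 80 / 0.8 = 100 enrolled.

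The figure reproduces. I use 40 per arm as the evaluable number. No rate, effect or power is given for silent aspiration, so everything below is assumption.

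**What a plain count contains.** Let p be baseline prevalence, s the probability that silent aspiration persists and o the probability of new onset. Later prevalence in an arm is p·s + (1 − p)·o. With p = 0.4, s = 0.75, o = 0.10 this is 0.30 + 0.06 = 0.36, so 0.30 / 0.36 = 83% of counted cases were there before treatment. With s = 0.60 and o = 0.20 it is 0.24 + 0.12 = 0.36 again: more resolution and twice the new onset give the same total.

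**Power, two-sided 5%, 40 per arm, 10,000 simulated trials per row** (simulation standard error at most 0.5 points). Each patient gets a baseline status with probability p, then a later status from s or o by arm. Mantel-Haenszel (MH, no continuity correction) and the exact conditional test are stratified by baseline status; Fisher and chi-square are not.

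| p | Control s / o | Acupuncture s / o | Fisher | Chi-square | MH | Exact stratified |
|---|---|---|---|---|---|---|
| 0.3 | 0.80 / 0.05 | 0.375 / 0.008 (OR 0.15) | 33.3 | 42.8 | 64.9 | 56.5 |
| 0.4 | 0.75 / 0.15 | 0.45 / 0.05 | 33.5 | 42.0 | 55.6 | 49.0 |
| 0.3 | 0.50 / 0.15 | 0.20 / 0.042 (OR 0.25) | 41.2 | 52.4 | 54.2 | 47.4 |
| 0.4 | 0.50 / 0.15 | 0.25 / 0.05 | 33.4 | 42.8 | 46.3 | 40.0 |
| 0.4 | 0.75 / 0.10 | same (no effect) | 2.7 | 4.8 | 4.6 | 3.1 |

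MH minus Fisher in the first four rows is 31.6, 22.1, 13.0 and 12.9 points. Exact stratified minus Fisher is 23.2, 15.5, 6.2 and 6.6. Chi-square minus Fisher, with no baseline information at all, is 9.5, 8.5, 11.2 and 9.4. That leaves 22.1, 13.6, 1.8 and 3.5 points of the MH gain due to baseline status itself.

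**Wider grid, 40 per arm, 60 scenarios with an effect.** Baseline prevalence 0.2, 0.3 or 0.5; control s / o of 0.5/0.15, 0.6/0.10, 0.7/0.05, 0.8/0.05 or 0.9/0.03; common odds ratio 0.4, 0.25, 0.15 or 0.08.

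- MH minus Fisher: 5 to 42 points, above 20 in 23 of 60.
- Exact stratified minus Fisher: 0 to 35 points, above 20 in 11 of 60.
- MH minus unadjusted chi-square: −1 to 34 points, above 20 in 9 of 60.
- With s = 0.5 and o = 0.15, MH minus Fisher never exceeds about 15 points. With s = 0.9 and o = 0.03 it reaches 42.

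At 50 per arm the ranges are similar: 3 to 44 points for MH and 2 to 38 for the exact test.

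**The case against.** Fisher's test is a recognised choice for small counts, and under 1:1 randomisation it keeps its error rate with or without baseline adjustment. Chance imbalance does move an unadjusted estimate: with s = 0.75 and o = 0.10 in both arms, a 10-point baseline imbalance shifts the risk difference by 10 × (0.75 − 0.10) = 6.5 points. The nominal error rate already allows for that. A difference between arms in later prevalence still reflects differential resolution or onset, only less efficiently. All of this stands, and it rules out calling the test biased.

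It may also be said that the article leaves incidence undefined, that the visit and at-risk set belong in a fuller document, and that incidence could mean new onset only. That stands too. The documents do not say that persistent and new cases are pooled, and the missing definition is not the point. The point is that the article fixes a particular test which, on any reading that includes patients positive at baseline, discards information the trial collects.

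Two stronger readings are tempting. A reader might infer that the main swallowing-safety comparison is affected. The documents do not call it that: PAS is the named safety measure, and silent aspiration is a separate analysis within a secondary outcome. A reader might also infer a fixed loss of more than 20 points of power. No rates are given from which to derive one; fewer than half of the grid scenarios exceed 20 points, and part of the gain comes from setting an asymptotic test against a conservative exact one.

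**Conclusion.** The point holds as a free improvement to a secondary safety analysis. The planned test is valid but ignores a baseline measurement that is likely to be prognostic, and its result would be hard to interpret if patients positive at entry are included. Under the assumed inputs at 40 per arm, stratification gains roughly 5 to 40 points of power over Fisher's test with Mantel-Haenszel, and 0 to 35 with an exact stratified test. The upper part of each range needs high persistence with low new onset and a sizeable treatment effect; with persistence near 50% the gain is modest and much of it is Fisher's conservatism. Even after the change, power stays limited in many of these settings, so a null result should not be taken as evidence of equal safety under either test.

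**What to change.** In section 2.12.2, replace Fisher's test for silent aspiration with a between-arm comparison at day 30 stratified by baseline silent-aspiration status (yes/no): Mantel-Haenszel, or an exact stratified test if a stratum is sparse. Report the risk difference with its confidence interval. Alongside it, show by arm and descriptively the number with new onset among patients free of silent aspiration at baseline, and the number resolved among those who had it. These counts are needed as well as the test, because effects in opposite directions in the two strata can cancel in a stratified test too.

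The cost is a change of analysis wording and a slightly longer table. It uses the planned baseline FEES and needs no new data or visits. The two descriptive counts will be small and should not be tested.

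### The only PAS-specific test ranks scores of 5 and above, a set that depends on treatment once patients are randomised, so the comparison loses power and can change direction

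*Protocol article*

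**What the plan says.** Section 2.9.2.4 lists PAS among the secondary outcomes as the measure of swallowing safety from FEES. On timing, section 2.10 says "FOIS, NIHSS, SWAL-QOL, PAS, and YPR-SRS will be assessed at baseline (pre-treatment), 15 and 30 days after treatment initiation", and also 30 and 60 days after treatment ends; Table 4 shows the same five visits.

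Three statements bear on the analysis:

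- Section 2.12.2, on silent aspiration: "The incidence of silent aspiration will be compared between groups using Fisher’s exact test". No PAS cut-off is attached.
- Section 2.12.2, next sentence, introduced as an addition to that test: "PAS scores ≥ 5 will be analyzed as ordinal variables using the Mann-Whitney U test".
- Section 2.12.5, for outcomes in general: "For primary and secondary efficacy outcomes, repeated-measures mixed-effects models or multiple linear regression will be employed". PAS is not named, and baseline PAS is not among the listed covariates.

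Table 5 defines the subgroups determined at baseline. None is based on PAS.

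**The concern.** Read plainly, the values that enter the rank test are those at 5 or above. At any visit after randomisation, membership of that set is itself an outcome. If an intervention takes a patient from 6 to 3, that patient drops out of the comparison and cannot count in its favour. The patients who stay are those who did not improve enough, and the two arms' remainders need not be alike.

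Two things are at stake. The test discards much of the sample, and with it the power to see a difference. And if one arm mainly helps patients at the lower end of the set, its remaining patients are on average worse, so the test can point against the arm that did better. In an open-label trial that presents PAS as one of its objective metrics, such a result on swallowing safety could mislead about either arm.

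**Working it through.** **Inputs.** The article gives no PAS figure to reproduce. It gives an arm size, used below. Section 2.7 states "These parameters (μA = 1.31, μB = 0.31, σ = 1.09, α = 0.05, power = 0.8, δ = 0.39", and then "After calculation, nA = nB = 40". With difference minus margin = 1.31 − 0.31 − 0.39 = 0.61:

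n per arm = 2 × 1.09² × (1.645 + 0.842)² / 0.61² ≈ 39.5, rounded up to 40, with one-sided α = 0.05 (two-sided would give 51). Total 80 / 0.80 = 100. The stated figures reproduce one-sided; they do not bear on the PAS point beyond supplying 40 per arm.

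**Assumptions.** The article does not define the PAS levels. I take a scale from 1 to 8 with higher scores worse. All PAS distributions below are assumed.

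**Example 1: direction.** Forty per arm. Control: 16 patients below 5, all placed at 4; 7 at 5; 7 at 6; 4 at 7; 6 at 8. Treatment moves 10 of the 14 patients at 5–6 down to 4 and changes nobody else, leaving 26 at 4, 2 at 5, 2 at 6, 4 at 7 and 6 at 8.

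| | Control | Treated |
|---|---|---|
| Mean, all patients | 217/40 = 5.43 | 202/40 = 5.05 |
| Patients at ≥ 5 | 24 | 14 |
| Mean among ≥ 5 | 153/24 = 6.38 | 98/14 = 7.00 |
| Median among ≥ 5 | 6 | 7 |
| Scores 7–8 among ≥ 5 | 10/24 = 42% | 10/14 = 71% |

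All patients favour treatment; the restricted set favours control. Neither Mann-Whitney test is significant (p about 0.12 each), so this shows a change of direction and no more. Placing everyone below 5 at exactly 4 is a simplification. It affects the all-patient means only; the figures among scores ≥ 5 do not depend on it.

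**Example 2: scores spread over the whole scale.** Counts for PAS 1 to 8: control 2, 4, 5, 5, 7, 7, 5, 5; acupuncture 8, 8, 7, 5, 1, 2, 4, 5.

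- All 80 patients: PAS ≥ 5 in 24/40 = 60% against 12/40 = 30%; medians 5 and 3; probability that an acupuncture patient scores better than a control patient (ties counted half) 0.65; p = 0.019 for acupuncture.
- Scores ≥ 5 only, 24 against 12 patients: medians 6 and 7; the same probability 0.31; p = 0.064, now towards control.

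**Simulation.** 4000 runs, 40 per arm, two-sided 5% tests. Control probabilities for PAS 1 to 8: 0.05, 0.10, 0.12, 0.13, 0.20, 0.15, 0.13, 0.12, so 60% are at ≥ 5. A patient who responds improves by 3 points, to no lower than 1; nobody is harmed.

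| Chance of response | Full scale, significant for acupuncture | ≥ 5, significant for acupuncture | ≥ 5, wrong direction | ≥ 5, significant for control |
|---|---|---|---|---|
| 30% at 1–4, 80% at 5–6, none at 7–8 | 60% | 0% | 97% | 46% |
| 30% at 1–4, 60% at 5–6, 10% at 7–8 | 48% | 0.2% | 82% | 15% |
| 50% at every level | 77% | 8% | 27% | 0.6% |
| 30% at every level | 34% | 4% | 39% | 1.2% |
| No effect | 2% | 3% | 49% | 2% |

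In the last row there is no true direction, so about half the runs point each way, and the ≥ 5 test keeps a total error of about 5%. In the third row about 14 acupuncture and 24 control patients are analysed. With 50 per arm the pattern is the same: row one gives 70% against 0%, with 56% significant for control; row three gives 85% against 10%.

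**The case against.** The strongest reply is that this sentence is not the whole PAS analysis. PAS is a secondary outcome, so the general sentence in section 2.12.5 reaches it with no cut-off, and a repeated-measures model could use the baseline visit. Silent aspiration is compared separately. The ≥ 5 sentence reads as an addition. This stands in part: a reader might infer that PAS will be compared only among scores of 5 and above, or that baseline PAS goes unused, and the article does not support either. But the general sentence does not name PAS, list its baseline value as a covariate or withdraw the ≥ 5 rule, which remains the only PAS-specific test.

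A second reply is that something else was meant. A subset defined by PAS ≥ 5 at baseline would be free of this bias. A yes/no endpoint at 5 would involve no selection either, and one should not call Mann-Whitney the wrong test for it: on a binary variable with tie correction it is essentially the 2 × 2 chi-square test. Both readings are possible intentions, but the text states neither. It speaks of ordinal variables, and Table 5 has no PAS subgroup.

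A third reply is that the article condenses a fuller plan. That would excuse an omission; here a rule is stated.

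Two further inferences are tempting and unsupported. The article does not say that a score of 5 marks aspiration, so one may say that a score fell below 5, not that treatment stopped aspiration. Nor does it make PAS the main check on FOIS: YPR-SRS has equal standing in section 2.9.2.4, and section 2.11 adds blinded assessors, recorded FEES and automatic sEMG recording.

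**Conclusion.** The defect holds. As written, the PAS-specific test selects on a post-randomisation outcome, so it is not a comparison of the randomised arms.

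Loss of power appears in every effective-treatment scenario tried, for example 77% to 8% with equal benefit at all levels. A reader might infer that reversal is the expected result. It is not: it becomes likely when benefit is concentrated at the milder scores among those ≥ 5, and with no effect the error rate is preserved. All these sizes rest on assumed PAS distributions and response patterns.

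The matter is one test of one secondary outcome, and the primary FOIS analysis is untouched. It should be corrected, but does not threaten the trial's main conclusion.

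**What to change.** Replace the ≥ 5 sentence in section 2.12.2 with three statements:

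1. The full PAS scale is compared between arms in all randomised patients at a named visit, such as day 30. The same Mann-Whitney test is enough; an ordinal model adjusted for the baseline PAS already collected is an alternative.
2. The proportion with PAS ≥ 5 (yes/no) is reported as a supplement, with all randomised patients as denominator.
3. Any subset with PAS ≥ 5 is defined by the baseline score only.

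If a baseline subset or a dichotomy was intended all along, saying so removes the problem. The cost is wording in the analysis section; no new data, visits or patients are needed.

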#### Analysis adjusting for treatment expectations

2.12.3

For the primary efficacy outcome (FOIS) and key secondary subjective measures (SWAL-QOL, PRO), analysis of covariance (ANCOVA) or mixed-effects models will be employed, with the total baseline treatment expectation score included as a covariate to control for its potential influence on treatment outcomes.

#### Analysis of Deqi

2.12.4

Group comparisons will be performed based on the binary classification of “adequate” versus “inadequate” deqi, with the Deqi Quality Index (DQI) included as a covariate in an analysis of covariance (ANCOVA) to assess therapeutic effects. Additionally, a linear mixed-effects model will be employed to examine the significance of the DQI × time interaction.

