**FIGURE 2 F2:**
[figure not shown]
Location of acupuncture points (Source: Atlas of meridians and acupuncture points by JiuDaifu).

**TABLE 2 T2:** Anatomical location of selected acupoints.

Acupoints	Location
GB20 (Fengchi)	In the posterior region of the neck, under the occiput, in the depression between the upper part of the sternocleidomastoid muscle and the upper part of the trapezius muscle.
GB12 (Wangu)	On the neck, at the posterior and inferior depression of the mastoid process behind the ear.
TE17 (Yifeng)	On the neck, behind the earlobe, at the anterior and inferior depression of the mastoid process.
CV23 (Lianquan)	In the anterior region of the neck, on the anterior median line, above the laryngeal prominence, and in the depression of the upper edge of the hyoid bone.

Patients will lie in a supine position. GB20 (Fengchi) needles will be bilaterally inserted at a 30° inferior angle toward the thyroid cartilage to a depth of 2.5–3.0 cun (≈65–75 mm). Small-amplitude, high-frequency twisting manipulation will be applied for 1 min to achieve strong stimulation, targeting a throat numbness/swelling sensation called “deqi.” GB12 (Wangu) and TE17 (Yifeng) will be needled with the same depth, angle, and technique as GB20. CV23 (Lianquan) will be inserted to 1.0–1.5 cun (≈25–40 mm) with lifting-thrusting manipulation. All needles will be retained for 30 min. Participants will receive three sessions per week for four consecutive weeks.

Deqi will be assessed subjectively using the Chinese version of the Massachusetts General Hospital Acupuncture Sensation Scale (c-MASS) (20), which evaluates 12 distinct sensations to quantify deqi intensity and quality. Participants will self-complete the c-MASS within 30 s after each needle manipulation. In accordance with prior domestic research (21), “adequate deqi” will be defined as a total c-MASS score ≥ 4, accompanied by at least two typical sensations (soreness, numbness, fullness, or heaviness) each rated ≥ 3. Cases not fulfilling both criteria will be classified as “inadequate deqi.” The Deqi Quality Index (DQI) for each participant will be calculated as the mean of the total c-MASS scores recorded at three time points: initiation of intervention, 15 and 30 min.

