#### Predefined subgroup analysis

2.12.6

Subgroup analyses will be prespecified in accordance with subgroup data reporting guidelines (49), with details provided in Table 5 (50–54). The results, which will be Bonferroni-corrected for multiple comparisons, will be reported as secondary exploratory outcomes. Treatment effect differences between the acupuncture and rehabilitation control groups across subgroups will be presented using forest plots.

**TABLE 5 T5:** Predefined subgroup categories and rationale.

Subgroup category	Stratification basis (determined at baseline)	Theoretical rationale
Baseline FOIS score subgroup	Low-level group (FOIS = 2), Medium-level group (FOIS = 3–4)	The severity of baseline swallowing function may affect intervention response. Patients with FOIS = 2 and those with FOIS = 3–4 have different therapeutic goals (e.g., prioritizing “oral feeding safety” for FOIS = 2 vs. “feeding independence” for FOIS = 3–4) (50).
Stroke subtype subgroup	Cortical infarction group, subcortical infarction group	Different infarction locations cause varying degrees of damage to the swallowing neural circuit: cortical infarction primarily impairs the cortical swallowing center, while subcortical infarction affects the cortico-brainstem pathway, which may lead to differences in the regulatory effect of acupuncture (51).
Age subgroup	Young group (18–60 years), Elderly group ( > 60 years)	Elderly patients often exhibit atrophy of swallowing muscles. This anatomical change may result in a slower response to the “neuroregulatory effect” of acupuncture compared to young patients (52).
Baseline NIHSS score subgroup	Mild neurological deficit group (NIHSS ≤ 8), moderate neurological deficit group (NIHSS = 9–16)	Stroke severity is correlated with the prognosis of dysphagia. Patients with moderate neurological deficits may require a higher intensity of intervention to achieve meaningful improvements in swallowing function (53).
Deqi adequacy subgroup (acupuncture group only)	Adequate Deqi group (DQI ≥ 4 and ≥ 2 typical sensations with score ≥ 3), inadequate Deqi group (participants who fail to meet the above criteria)	Deqi is a key link in the efficacy of acupuncture. Adequate Deqi (characterized by typical sensations such as soreness, numbness, distension, and heaviness) may enhance the activation of the swallowing neural circuit, thereby strengthening the therapeutic effect of acupuncture (54).

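### The exploratory deqi analysis adjusts the adequate/inadequate contrast for the DQI that largely defines it, and the ≥ 4 cut-off is applied to two different quantities

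*Protocol article*

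**What the plan says.** Four statements bear on this point.

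- **Model (2.12.4).** Adequate and inadequate deqi are compared, "with the Deqi Quality Index (DQI) included as a covariate in an analysis of covariance (ANCOVA) to assess therapeutic effects". The next sentence adds a linear mixed-effects model that tests DQI × time.
- **Adequacy in the methods (2.8.1).** Adequate deqi "will be defined as a total c-MASS score ≥ 4, accompanied by at least two typical sensations", each of those sensations rated at least 3. No time point is attached to the total.
- **Adequacy in the subgroup table (2.12.6, Table 5, acupuncture group only).** "Adequate Deqi group (DQI ≥ 4 and ≥ 2 typical sensations with score ≥ 3". Here the cut-off is placed on the DQI, which 2.8.1 defines as the "mean of the total c-MASS scores recorded at three time points: initiation of intervention, 15 and 30 min".
- **Collection (2.8.1).** "Participants will self-complete the c-MASS within 30 s after each needle manipulation". The manipulation described for GB20, GB12 and TE17 lasts 1 minute, lifting-thrusting is described for CV23, and then "All needles will be retained for 30 min". No manipulation at 15 or 30 minutes is described.

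Section 2.12.6 labels the subgroup results as secondary and exploratory.

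**The concern.** A binary class formed mainly by cutting a continuous score carries mostly the information in that score. With both in one ANCOVA, the class coefficient no longer estimates how adequate patients differ from inadequate ones. It estimates only a jump at the cut-off over and above the straight-line relation with the DQI. Table 5 justifies the subgroup by the idea that adequate deqi may strengthen the treatment effect. If benefit rises steadily with deqi intensity, that idea is right, yet the adjusted contrast would show nothing.

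The second problem is that the class is not uniquely defined. A single total and a three-time mean are different quantities, so the groups being compared depend on which definition the analyst takes. If that stays open until the data are in, it becomes a post hoc choice.

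**Working it through.** The plan gives no figure for the deqi analysis, so there is none to reproduce.

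**1. Adjusting the class for the DQI**

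Inputs. Outcome SD 1.09 and 40 evaluable patients per arm come from 2.7. The rest is assumed: DQI ~ N(4, 1.5); adequacy taken as DQI ≥ 4 alone, without the sensation rule; slope 0.36 FOIS points per DQI point.

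- With the cut at the mean, the mean DQI of the two classes differs by 2 × 1.5 × √(2/π) = 2.39.
- Expected unadjusted contrast under linearity: 0.36 × 2.39 = 0.86.
- Correlation of class with DQI: √(2/π) = 0.80. Variance inflation from adjustment: 1/(1 − 2/π) = 2.75, so the standard error rises by a factor of about √2.75 = 1.66.
- Expected adjusted class coefficient under linearity: 0, because the line in the DQI already accounts for the whole difference.

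Simulation (4,000 runs, two-sided 5% tests):

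| Truth | Unadjusted contrast | Detected | DQI-adjusted contrast | Detected |
|---|---|---|---|---|
| Linear, 0.36 per DQI point | 0.87 | about 64% | about 0 | 5% |
| Threshold effect of 0.87 at DQI 4 | 0.87 | 68% | 0.88 | 30% |

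Under linearity the standard error rises from 0.37 to 0.60.

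Sensitivity under linearity (n = 40 or 50, 50% or 70% adequate, slope 0.6 per SD of DQI). With a pure DQI cut, the unadjusted contrast is 0.93 to 0.98 (66% to 81% detected) and the adjusted one about 0 (4% to 5%). With adequacy only partly determined by the DQI, which is closer to Table 5 with its sensation rule, the variance inflation drops to between 1.4 and 2.1 and the unadjusted contrast to between 0.65 and 0.87. The adjusted contrast is still about 0.

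**2. The two cut-offs**

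Take totals of 6 (two typical sensations at 3), 3 and 1 at 0, 15 and 30 minutes.

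- Under 2.8.1, at insertion: 6 ≥ 4 and two sensations at 3, so adequate.
- Under Table 5: DQI = (6 + 3 + 1)/3 = 3.33 < 4, so inadequate.

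More generally, if a fraction f of the insertion total T persists at both later times, DQI = T(1 + 2f)/3, and DQI ≥ 4 needs T ≥ 12/(1 + 2f). For T = 6 this means f ≥ 0.5. Below that the two definitions disagree.

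If the total is the plain sum of the items, which the article does not state, two sensations rated at least 3 already give 3 + 3 = 6. The ≥ 4 condition in 2.8.1 then never decides a case, whereas in Table 5 it can.

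**3. Collection timing**

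One sentence of 2.8.1 ties the form to needle manipulation. Another has totals "recorded at three time points: initiation of intervention, 15 and 30 min". The text describes no manipulation at the two later times, so the two sentences do not yet fit together.

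**The case against.** The strongest reply is that the simulation partly builds in its answer: if benefit is generated as a straight line in the DQI, the adjusted class effect is zero by construction. That is fair. Table 5's rationale is equally compatible with a threshold, and then adjustment causes no bias. But detection still drops from 68% to 30%, so the planned model is the worse choice under either truth. Taking adequacy as a pure DQI cut is also the extreme case; the partial-determination runs soften the variance inflation but not the vanishing contrast under linearity.

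A second reply is that the plan has another route to a dose-response finding. This stands: the DQI × time model uses the continuous score and is untouched. Section 2.12.6 also does not itself call for DQI adjustment of the subgroup.

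A third is that 2.8.1 can be read as a rule for a single reading and Table 5 as its participant-level form, and that the deqi data go into the CRF, so either class can be derived centrally. This also stands, and it makes the conflict repairable. It does not say which class 2.12.4 uses.

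A reader might infer that the analysis cannot be run, or that the 15- and 30-minute scores will not exist. The documents support neither. The ANCOVA is estimable, because Table 5's class is not an exact linear function of the DQI, and 2.8.1 says that totals are recorded at those times. Nor does the text say that manipulation happens only once; a condensed article may leave that to the full protocol.

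**Conclusion.** The point holds as a defect of interpretation and definition in an exploratory analysis within the acupuncture arm. The sentence in 2.12.4 does not affect the comparison of acupuncture with rehabilitation on FOIS.

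The planned ANCOVA would lose a contrast of about 0.87 points entirely if benefit is linear in the DQI, or cut its detection by more than half (68% to 30%) if there is a true threshold. These sizes rest on an assumed DQI distribution, an assumed slope or step, and adequacy as a pure DQI cut; only the SD and the arm size come from the protocol. That the class is adjusted for its own parent variable follows from 2.12.4 and Table 5 alone.

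The conflict between 2.8.1 and Table 5 also holds without any distributional assumption. Only the statement that ≥ 4 never binds in 2.8.1 depends on a sum score. The timing of the c-MASS form is a minor inconsistency. The change is worth making before analysis but is not critical to the trial.

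**What to change.** - **2.12.4:** do not enter the binary class and the DQI in the same model. Make the continuous DQI within the acupuncture arm the main deqi analysis, and show the adequate/inadequate contrast without DQI adjustment. The DQI × time model can stay as it is.
- **2.8.1 and Table 5:** use one adequacy definition in both, applied to one named quantity (a total at a stated time, or the DQI). State how the c-MASS total is formed, and if it is a sum, review whether the ≥ 4 condition does anything.
- **2.8.1, minor:** reconcile the completion rule with the DQI, either by stating that the form is also completed at 15 and 30 minutes or by defining the DQI from the post-manipulation score only. This concerns the form and the index, not the needling procedure.

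The cost is wording in three places. If the form is confirmed at 15 and 30 minutes, that means at most two further short self-ratings per session, which the DQI definition already presupposes.
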